**Principle Investigator: [name].**

**Co-Investigators: [name].**

**[name].**

**[name].**

**[name], M.Sc.**

**[name].**

**1.0 Rationale**

Currently in Canada, trends indicate that there is an increasing number of aging Canadians with longer life spans^1^. Thus, there is a greater need to identify and understand the underlying physiological mechanisms of the aging process. One area of interest revolves around understanding the significant decline in lean muscle mass and strength as we age. These phenomena are referred to as sarcopenia and dynapenia, respectively, and can have profound negative effects on muscle function and overall health. Sarcopenia and dynapenia accelerate the progression of various chronic diseases such as type 2 diabetes and cardiovascular disease, and lead to an increased incidence of injuries^2^. Consequently, the search for the best therapeutic strategy to counterbalance the loss of muscle mass and strength is ongoing.

Aged muscle, similarly to young muscle, retains the ability to positively respond to a physiological stimulus such as resistance exercise (RE)^3^. The result is that older adults who lift weights are capable of increasing both their strength and muscle mass, facilitating their ability to perform day-to-day activities, such as lifting heavy grocery bags and climbing stairs. Thus, continued regular exercise is currently the best therapeutic strategy to improve mobility and counteract the loss of muscle. Recently, our group demonstrated that similarly to RE, a bout of high-intensity interval exercise (HIIT) was able to generate a significant anabolic response in a group of older men. Namely, HIIT significantly stimulated muscle protein synthesis (MPS), as well as elicited a satellite cell response up to 48 hours post-exercise (unpublished results). These observations lead us to speculate that a training program combining HIIT, which consists of repeated bouts of vigorous aerobic exercise interspersed with period of rest, and RE might induce favourable changes in body composition and physical function in older men.

Despite the responsiveness of older muscle exercise, studies suggest that older muscle requires greater nutritional support compared to younger muscle. For instance, older men require ~40g whey protein to maximally stimulate MPS, whereas younger men only require ~20g^4^. This nutritional ‘anabolic resistance’ of older muscle can be alleviated with dietary strategies. Increased protein intake, particularly when combined with exercise training, is effective in bolstering muscle mass^5^. Further, creatine^6^, calcium^7^ and vitamin D^8^ have been shown to independently increase strength in older men, and omega-3 fatty acids have been shown to increase rates of MPS in older adults^9^ It is possible that a protein-based supplement that contains creatine, calcium, vitamin D and omega-3 fatty acids may exert an additive or even synergistic effect on muscle mass and strength, particularly if combined with a progressive exercise training program. To date, however, no one has tested this hypothesis.

**2.0 Objectives**

This study will examine the effects of a 12 week RE + HIIT exercise training program combined with multi-ingredient protein-based supplementation (SUPP), compared to 12 weeks of training combined with placebo (PLB), in older men. The substantive objectives of this study are to determine:

1. Primarily, whether the supplement is able to enhance exercise-mediated changes in muscle strength, physical function and body composition.
2. The acute satellite cell response to a single bout of HIIT + RE following 12 wks of protein or placebo supplementation.
3. The effect of each intervention on:
   1. Glucose metabolism and fasting serum lipids.
   2. Cognitive and executive function
   3. Renal function.

**3.0 Hypotheses**

1. Supplementation and exercise training will independently and synergistically increase muscle strength and physical function, as well as augment fat-free mass (FFM) and reduce fat mass (FM).
2. The acute satellite cell response will be greater/less impaired after 12 weeks of protein supplementation compared with placebo.
3. Myofibrillar and sarcoplasmic MPS, glycemic control, lipid partitioning, executive function and quality of life will improve in response to supplementation + exercise and exercise alone, and to a lesser extent following supplementation alone. Neither supplementation nor placebo training will alter renal function.

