**5.0 Sample size**

A total of 50 old, active men will be recruited; participants will be separated into 2 groups of 25 and each group will receive either SUPP or PLB. Previous studies have shown that supplementation with creatine monohydrate during RE training in older adults can increase dynamic strength by approximately 1.75 – 3.25 kg more than RE training alone. Using this effect size and a standard deviation of 1.5 kg, n = 20 subjects are needed to detect a difference with α = 0.05 and β = 0.8 using a two-way ANOVA. To account for the possibility of increased variability in the sample set and allowing for a potential 20% dropout rate, a conservative number of 25 subjects per group was chosen.

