| Global cognitive ability | - Montreal Cognitive Assessment (MoCA)^10^ - National Adult Reading Test (NART)^11^ |
| Language | - Boston Naming Test (BNT)^12^ - Controlled Oral Word Association Test^13^ |
| Memory | - Face recognition memory paradigm^14,15^ - Hopkins Verbal Learning Test –Revised (HVLT-R)^16^ - Brief Visual Memory Test - Revised (BVMT-R)^17^ - Rey Complex Figure Test, Wechsler Memory Scale – Revised - Logical Memory subtest, Autobiographical Interview – Abbreviated Administration^18^ |
| Attention | - Wechsler Adult Intelligence Scale – 3^rd^ Edition (WAIS-III) Digit Span Subtest^19^ |
| Inhibitory control | - Erikson Flanker Task^20^ |
| Working memory | - Directed Forgetting Test^21^ |

We will evaluate quality of life with a series of questionnaires designed to explore sleep quality, stress levels, daily activities, geriatric depression and subjective memory.

*7.8 Renal function*

We will estimate GFR using serum cystatin C concentrations. This will be measured using the fasting blood samples collected during the OGTTs performed at pre, mid (week 7) and post-study (week 19) testing.

*7.9 Diet analysis and physical activity*

Participants will complete a 3-day food diary and PA log during each assessment week. They will record everything the eat and drink, as well as any exercise they engage in, for 2 week days and 1 weekend day. Additionally, participants will wear and accelerometer (mounted on an armband) for the same 3 days so that we may estimate daily energy expenditure. The 3-day food diary, PA log and accelerometer will allow us to approximate daily caloric intake and macronutrient distribution, as well as to determine whether their dietary and activity patterns have changed throughout the course of the study.

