**9.0 Data analysis**

Data will be analyzed using a 2-way analysis of variance (ANOVA) with between (SUPP, PLB) and within (time) group comparisons. Tukey’s HSD post hoc testing will be used to assess differences between the means when interactions are detected. Statistical significance will be accepted at α<0.05.

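### The renal hypothesis predicts no change, but the only stated analysis is a difference test, so only a non-significant result can agree with it

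*Protocol*

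**What the plan says.** Section 2.0 of the protocol lists renal function as the last sub-item of the third objective, in neutral terms: "The effect of each intervention on" several outcomes, of which renal function is one. Section 3.0 then commits to a direction, or rather to the absence of one: "Neither supplementation nor placebo training will alter renal function".

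Section 7.8 defines the measure: "We will estimate GFR using serum cystatin C concentrations", from fasting samples "collected during the OGTTs performed at pre, mid (week 7) and post-study (week 19) testing".

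Section 9.0 gives a single method for everything: "Data will be analyzed using a 2-way analysis of variance (ANOVA) with between (SUPP, PLB) and within (time) group comparisons". Tukey's "post hoc testing will be used to assess differences between the means when interactions are detected", and "Statistical significance will be accepted at α<0.05".

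Section 5.0 bases the sample size on strength only: creatine with resistance training "can increase dynamic strength by approximately 1.75 – 3.25 kg more than RE training alone", with an SD of 1.5 kg. It arrives at 20 subjects and raises this to 25 per group, citing 20% dropout. No figure in the section concerns eGFR.

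**The concern.** For strength, body composition and most other outcomes the protocol predicts an effect, and a difference test suits that: rejecting the null supports the prediction. For renal function the prediction is the null. Rejection would contradict it, and non-rejection is the only outcome that agrees with it. Dropout, assay noise and small numbers all push towards non-rejection, so weaker data would look more favourable to the hypothesis.

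The post hoc rule adds a gap. If eGFR fell equally in both arms there would be no interaction, so no pairwise comparison would follow, although the hypothesis concerns both arms. Such a fall could appear only as a main effect of time.

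At stake is what the trial can say about the kidney in men aged 70 or older who take a protein-based supplement. A statement that renal function was not altered, resting on p > 0.05, could be relied on without the data having excluded a change of any particular size.

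**Working it through.** **The plan's own sample size (section 5.0).** Inputs: difference 1.75 to 3.25 kg, SD 1.5 kg, alpha 0.05 (taken as two-sided), and a stated β of 0.8, read as 80% power.

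- Per-group n = 2 × (1.960 + 0.842)² × (SD/difference)².
- At 1.75 kg: 2 × 7.85 × (1.5/1.75)² = 11.5, so 12 (13 with the t distribution). At 3.25 kg: 3.3, so 4 (5 with t).
- The stated 20 does not reproduce at 80% power, per group or as a total (24 to 26 at 1.75 kg). It matches about 95% power at 1.75 kg: 2 × (1.960 + 1.645)² × 0.735 = 19.1, so 20. This is a separate matter, errs on the cautious side, and does not affect the renal point.
- The dropout step reproduces: 20 / (1 − 0.20) = 25. About 20 completers per group are therefore expected.

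**Precision for eGFR change, in units of its SD, with 20 completers per group.**

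- Between arms: t(0.975, 38) × √(2/20) = 2.024 × 0.316 = 0.64 SD. With all 25 retained it is 0.57 SD.
- Within one arm: t(0.975, 19) / √20 = 2.093 / 4.472 = 0.47 SD.

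**Chance that a real between-arm difference is non-significant** (two-sample t test, two-sided 0.05, 20 per group).

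| True difference | Power | Non-significant |
| --- | --- | --- |
| 0.2 SD | 0.095 | about 90% |
| 0.5 SD | 0.34 | about 66% |
| 0.8 SD | 0.69 | about 31% |

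With 25 per group, the figure for 0.5 SD is 59%. Power of 80% is reached only at 0.91 SD with 20 per group (0.81 SD with 25).

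**In eGFR units.** The protocol gives no SD, so a range of 6 to 15 mL/min/1.73 m² for the SD of change is assumed.

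| Assumed SD | Half-width between arms | Half-width within an arm |
| --- | --- | --- |
| 6 | 0.64 × 6 = 3.8 | 0.47 × 6 = 2.8 |
| 10 | 6.4 | 4.7 |
| 15 | 9.6 | 7.0 |

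The two-sample comparison of change is a simple stand-in for the group-by-time interaction over three visits. Adjusting for baseline may narrow the between-arm interval somewhat.

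**The case against.** Four objections carry weight.

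- **The protocol states no rule for reading the renal result.** A reader might infer that non-significance is to be taken as evidence of renal safety, and that this is the trial's safety objective. The text supports neither. It speaks of renal function, places it third among the objectives beside lipids and cognition, and does not mention the kidney under section 8.0, Risks. What stands is narrower: the stated hypothesis and the stated test leave no other result that could agree with the prediction.
- **Margins and interval reporting are commonly left to a statistical analysis plan, which is not shown.** Their absence from the protocol is therefore not the point. The point is the pairing of a no-effect hypothesis with a difference test for all data, both of which the protocol states. ANOVA does not prevent the reporting of estimates and intervals, so the repair fits within the planned analysis.
- **The hypothesis is about change in each arm, and the within-arm comparison is more precise.** This is correct, and is why both half-widths are given. The between-arm figure alone would overstate the imprecision for the hypothesis as written. The logical fault is the same for either contrast.
- **The eGFR figures rest on an assumed SD.** This is also correct. The results in SD units do not depend on it, but whether 0.64 SD is a large or small change in eGFR cannot be settled from the protocol.

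**Conclusion.** The point holds as a mismatch between the section 3.0 hypothesis and the section 9.0 test, for a third-tier objective. Non-significance is the only result that can agree with the hypothesis. With about 20 completers per group it is the likelier result even if the arms truly differ by 0.5 SD (about 66%).

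This rests on 20% dropout, a two-sided 0.05 test and a common SD of change in the two arms. The conversion to mL/min/1.73 m² rests on the assumed range of 6 to 15.

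It might be inferred that the remedy is a one-sided non-inferiority test of SUPP against PLB at week 19. The documents do not support that either. The hypothesis covers change in both directions and in both arms, so an equal fall in each would pass such a test. Week 7, the end of the supplement-only phase, would also be left out.

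**What to change.** For cystatin-C eGFR, report the change within each arm and the baseline-adjusted SUPP–PLB difference, at weeks 7 and 19, each with a 95% confidence interval. State that no alteration will not be concluded from p > 0.05. Then choose one of two courses:

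- treat the renal result as descriptive; or
- claim no meaningful change only if the interval lies within a justified range fixed before unblinding, and otherwise report that a meaningful change is not excluded.

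The cost is a few sentences in the protocol or analysis plan and, for the second course, the work of justifying the range. No extra samples or visits are needed. The downside is that the renal result may have to be reported as inconclusive. As an illustration, excluding a between-arm difference of 0.5 SD in one direction only, at one-sided 0.025 with 80% power, needs 2 × 7.85 / 0.5² = 62.8, so 63 per group. The descriptive course therefore fits this trial's size more easily.

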**4.0 Population under study**

For this study, we will recruit 50 sedentary yet healthy men aged 70 years or older (n=25 per group). Participants will be considered sedentary if they have not participated in a structured resistance or aerobic training program in the past 6 months. In addition, participants will have a BMI in the normal or overweight range (18.5 – 30.0 kg/m^2^), will have been weight stable for the past 6 months, and will present with a normal resting blood pressure or stage I hypertension at screening (SBP < 140 – 159 mmHg; DBP < 90 – 99 mmHg).

The following exclusion criteria exist to ensure the safety of participants and that certain outcome measures are not confounded:

- Smoking
- Use of simvastatin or atorvastatin
- Use of non-steroidal anti-inflammatory drugs
- Injuries that prevent safe participation in an exercise program
- Prescription blood-thinners
- Diabetes or other metabolic disorders
- Cardiac or gastro-intestinal problems
- Infectious disease or cancer

*4.1 Screening*

A variety of questionnaires and physiological tests will be used to assess eligibility for the study:

Medical Screening Questionnaire and Physical Activity Readiness Questionnaire (PAR-Q): Members of the research team will help potential participants complete a health questionnaire, which will assess the potential participant’s age, physical activity levels, and any medications and medical conditions that the individual may have. We will also measure height and weight. Potential participants must answer ‘no’ to all questions on the PARQ.

OGTT: Potential participants will also undergo a 2 hour 75g OGTT to determine whether they are diabetic (fasting blood glucose > 7.0 mM; 2 hour blood glucose > 11.1 mM) or display impaired glucose tolerance (fasting blood glucose > 5.6 mM; 2 hour blood glucose > 7.8 mM). Details of the OGTT protocol are described below.

Blood pressure: Systolic and diastolic blood pressure must be within the range indicated above in order for an individual to participate in this study. Participants will quietly rest in the supine position for 5 min before measurements are made using an automatic blood pressure cuff. A total of 3 measurements will be made, and the average will be used to assess resting blood pressure.

Exercise stress test: Participants must demonstrate normal cardiac function during a graded, maximal exercise stress test on a cycle ergometer using a 12-lead ECG. All exercise stress tests will be conducted at the 3U Cardiorespiratory Clinic at McMaster University Medical Centre, under the supervision of a trained technician.

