**6.0 Design**

The overall study design is depicted in Figure 1, below. Participants will be placed in either the SUPP or PLB group, depending on their strength, fat-free mass and body mass index.

[figure not shown]

**Figure 1**. Study schematic. D_2_O, deuterium oxide; 1RM, 1 repetition maximum; VO_2peak_, peak oxygen consumption; OGTT, oral glucose tolerance test; QOL, quality of life assessment, PA, physical activity

*6.1 Assessments*

Approximately 1 week prior to beginning the study, participants will receive a muscle biopsy from *vastus lateralis*, exercise and physical function testing, body composition analysis, an OGTT, and an executive function and quality of life assessment (see Figure 1). These tests will take place over the course of 3-5 days during the same week. During the week these assessments are taking place, participants will complete a 3-day food diary and physical activity log at home, as well as wear an accelerometer (mounted on an arm band) to estimate daily caloric intake, macronutrient distribution and energy expenditure. We will assess glomerular filtration rate (GFR), an estimate of kidney function, by examining cystatin C concentrations in blood samples collected during pre, mid and post-study testing periods.

These assessments will be repeated during week 7, and again upon completion of the study during week 19. Exercise tests (1RM and VO_2peak_) will be repeated at weeks 11 and 15 to ensure an adequate exercise stimulus is maintained during training. The assessments at week 7 and week 19 include serial muscle biopsies for the measurement of the acute satellite cell response to exercise. Details of the serial muscle biopsy protocol are described below. Participants will be asked to refrain from strenuous exercise, caffeine and alcohol for 48 hours prior to each assessment.

*6.2 Phase 1*

Phase 1 of the study is 6 weeks in duration and will be completed primarily at home. Participants will consume 2 study beverages per day – the first approximately 1 hour after breakfast, and the second before bed. Participants will be encouraged to maintain their normal diets and levels of physical activity. We will provide participants with all their study beverages at the beginning of the study.

*6.3 Phase 2*

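### Current users of creatine or protein supplements are not excluded or restricted, so they can enrol in either arm and may shrink the SUPP-PLB difference

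*Protocol*

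**What the plan says.** Section 4.0 gives the purpose of its exclusions as "The following exclusion criteria exist to ensure the safety of participants and that certain outcome measures are not confounded". The eight items cover smoking, certain drugs, injury and disease. None concerns a dietary supplement. Screening (section 4.1) asks about age, activity and "any medications and medical conditions that the individual may have"; supplements are not named.

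The product under test is described in section 1.0 as "a protein-based supplement that contains creatine, calcium, vitamin D and omega-3 fatty acids". The same section says that creatine, calcium and vitamin D "have been shown to independently increase strength in older men", and that extra protein combined with training helps to build muscle mass. Section 5.0 takes its effect size from creatine: 1.75 to 3.25 kg of dynamic strength beyond training alone.

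Section 6.0 places men in SUPP or PLB "depending on their strength, fat-free mass and body mass index". Section 6.2 (Phase 1) says "Participants will be encouraged to maintain their normal diets and levels of physical activity" and mentions neither a washout nor the men's own supplements. Section 7.9 provides for monitoring: "Participants will complete a 3-day food diary and PA log during each assessment week". Section 7.6 measures 25-hydroxyvitamin D in fasting blood.

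**The concern.** The supplement is the only planned difference between the two groups. For the other factor in the first hypothesis, exercise, section 4.0 secures a clean starting point by requiring no structured training in the past 6 months. For the supplement there is no equivalent requirement. The exclusion of two statins and of anti-inflammatory drugs shows that concomitant agents were considered, but the test ingredients do not appear.

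A man who already takes creatine or a protein powder is therefore eligible and may continue in either arm. If he is in SUPP, part of the benefit may already be present at baseline. If he is in PLB, he goes through the 12 weeks of training with an ingredient that the protocol itself regards as active. Both effects reduce the SUPP-PLB difference in the primary outcomes. With 20 to 25 men per group, users could also fall unevenly between the arms by chance. A null result would then be harder to read as absence of effect.

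**Working it through.** **Inputs.** From section 5.0: difference 1.75 to 3.25 kg (midpoint 2.5 kg), SD 1.5 kg, α = 0.05 (taken as two-sided), β given as 0.8 (read as power 0.80), n = 20 (per group by implication), dropout 20%. The share of men already using an active ingredient is not in the protocol, so 0 to 50% is assumed.

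**The plan's own figure.** The dropout step reproduces: 20 / (1 − 0.20) = 25 per group. The 20 does not. By the normal approximation, n per group = 2(1.960 + 0.842)² × 1.5² / 1.75² = 11.5, so 12 (13 by the t test). At the plan's own inputs, 20 per group therefore gives more than 80% power, which matters for the size of the present point.

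**Dilution model.** Suppose a fraction p of men in each arm has no supplement contrast left. The expected difference becomes Δ(1 − p), with the SD held at 1.5 kg. Power is for a two-sided two-sample t test with 20 per group; n per group for 80% power is by the normal approximation.

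| p | Difference from 1.75 kg | Power | n per group for 80% |
|---|---|---|---|
| 0 | 1.75 | 0.95 | 12 |
| 0.1 | 1.575 | 0.90 | 15 |
| 0.2 | 1.40 | 0.82 | 19 |
| 0.3 | 1.225 | 0.71 | 24 |
| 0.4 | 1.05 | 0.58 | 33 |
| 0.5 | 0.875 | 0.44 | 47 |

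**Break-even.** With 20 per group and SD 1.5 kg, the difference detectable with 80% power is 1.36 kg. Power falls below 80% when 1.75(1 − p) < 1.36, that is p > 1 − 1.36/1.75 ≈ 22%. From 2.5 kg the limit is 1 − 1.36/2.5 ≈ 45%; power there is 0.98 at p = 0.2 and 0.87 at p = 0.4.

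**Variant.** If only users in PLB gain the full effect, that arm becomes a mixture and the average SD rises to √(1.5² + p(1 − p)Δ²/2). At Δ = 1.75 kg and p = 0.2 this is √(2.25 + 0.16 × 3.0625/2) = 1.58 kg, with power 0.78; at p = 0.3 power is 0.65. The break-even is then slightly under 20%.

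**What p stands for.** The loss of mean difference is an upper bound, because each user is assumed to lose the whole contrast. The 1.75 kg is a creatine effect, so p fits creatine users best. A man who takes only protein, or only vitamin D, calcium or omega-3, still differs between arms in the remaining ingredients.

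**The case against.** The strongest reply is that the protocol makes no false statement. Its exclusions are said to protect certain outcomes, not to remove every source of variation, and supplement against placebo on top of usual intake is a coherent question. Several stronger readings that a reader might infer also fail:

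- *The placebo is contaminated.* Nothing suggests that the placebo product contains an active ingredient. The issue is what individual men take by themselves.
- *Men are told to keep taking their supplements.* Section 6.2 only encourages a normal diet, sits under Phase 1 and does not name supplements. It may equally discourage starting new ones.
- *Common use of vitamin D, calcium or fish oil removes the contrast.* Section 1.0 hypothesises that "a protein-based supplement that contains creatine, calcium, vitamin D and omega-3 fatty acids may exert an additive or even synergistic effect", so a user of one ingredient retains a contrast on the others. The creatine effect size cannot be applied to him.
- *Phase 1 suffers most.* Section 9.0 includes time as a within-person factor. A stable user in PLB carries his intake at baseline and should change little in Phase 1, like a non-user. Any dilution there comes through users in SUPP.
- *The trial is underpowered.* That depends on a prevalence that the protocol does not give, and the stated n has slack at its own inputs.

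It is also fair that the diary and the vitamin D measurement could reveal some use, and that the screening questionnaire, which is not shown, may ask about supplements. But these describe intake. None is tied to eligibility, and stable prior use would not show as a change in diet.

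What stands is the gap itself: creatine and protein users can enrol and continue. Eligibility and restrictions belong in the protocol and cannot be put right at analysis.

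**Conclusion.** The point holds as a cheap improvement to the design, not as a demonstrated failure. The direction is clear: background use of creatine or protein pulls the SUPP-PLB difference towards zero. The size is conditional. It rests on an assumed prevalence, on complete loss of contrast in each user, and on the lowest effect that section 5.0 quotes. Under those assumptions, use by 10% of men costs about 5 percentage points of power (0.95 to 0.90), and power stays at or above 80% up to about 22% (slightly under 20% in the mixture variant). At the 2.5 kg midpoint the main-model limit is about 45%. The documents do not support a claim that the primary comparison is invalid or that its power is inadequate.

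**What to change.** Three changes:

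1. In section 4.0, add current use of creatine or protein supplements to the exclusions.
2. In sections 6.2 and 6.3, ask participants not to start any of the five ingredients on their own initiative during the study.
3. In section 4.1, record use of vitamin D, calcium and omega-3 at screening, so that a sensitivity analysis can take account of it. Men who use only these remain eligible.

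Use of these three could also be added to the variables that guide group placement. This is optional, because it would be a fourth factor for 50 men.

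The cost is one eligibility line, one instruction and one questionnaire item. A few more men will be screened out, and the results will generalise slightly less well to current users. The sample size need not change.
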